**9.4 Compensation for health hazards**

The principal investigator and sub-investigator upon recognition of adverse events should perform appropriate treatment immediately and record the incidence in medical records.

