**Effects of brown rice or white rice on glycemic and lipid metabolism, and vascular function**

**1 Background**

We have been reported that high-fiber diet intervention with combination of brown rice and fiber-rich dishes improve endothelial function in patients with type 2 diabetes mellitus (T2DM)1,2. However, it remains unknown whether brown rice is an essential factor to improve endothelial function in these patients. In this study we hypothesized that a simple dietary intervention with brown rice will be acceptable dietary intervention in out-patients and improve vascular function through change in glycemic and lipid metabolism.

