**2 Study objectives**

To evaluate the effect of brown rice or white rice-based diet intervention on glycemic　and lipid metabolism, and vascular function.

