**Exclusion criteria**

1) Patients with severe vascular, hepatic, renal, cancer, and/or infectious disease

2) Patients who changes drug treatment within 2 months

3) Patients with rapid weight loss

4) Patients who enrolled in another study within 1 month

5) Patients who have eaten brown rice

6) Patients who have taken fiber supplement

7) Pregnancy and breast-feeding patient

8) Patients who have taken warfarin and NSAIDS

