**3.6 Study schedule (Figure 1)**

**3.6.1 Run-in period**

Eligible patients undergo a 4- to 8-week run-in period to maintain a stable diet and assess tolerability. Participants will be advised by a dietician to have a standard diet for diabetes, consisting of 28–30 kcal/kg of ideal bodyweight (protein 15%, fat 25%, carbohydrate 60%) at the beginning of the run-in period.

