**3.6.2 Intervention period (2 months)**

After the run-in period, participants will be randomly assigned to a brown rice or white rice diet. Both brown rice and white rice will be provided in small single-serve pouches for the 8-week study to limit energy intake. Participants will be instructed to consume provided pouches as a staple food for 10 out of 21 meals per week and to maintain energy intake at 28–30 kcal/kg for 8 weeks.

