**8 Discontinuation and interruption of study**

The principal investigator should determine whether continuation of the study can be justified when significant information regarding quality, safety are newly recognized.

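### After randomisation, adverse events go to medical records when recognised rather than being asked about and entered on the CRF, and no outcome is tied to the hypothesis that brown rice is acceptable

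*Protocol*

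**What the plan says.** **Adverse events.** Section 9.4 is the only adverse-event provision. Investigators "upon recognition of adverse events should perform appropriate treatment immediately and record the incidence in medical records". No CRF entry, routine question or collection window is given.

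**Hypoglycemia.** Section 3.9 asks for a CRF description when a drug is reduced, changed or withdrawn because of hypoglycemia during the run-in or intervention. It does not ask for episodes that change no drug.

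**Tolerability.** The term is used once, in section 3.6.1: "Eligible patients undergo a 4- to 8-week run-in period to maintain a stable diet and assess tolerability". During that time "Participants will be advised by a dietician to have a standard diet for diabetes". The pouches come later (section 3.6.2): "After the run-in period, participants will be randomly assigned to a brown rice or white rice diet". The exclusion criteria also list "Patients who have eaten brown rice".

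**Acceptability.** The Background hypothesises that "a simple dietary intervention with brown rice will be acceptable dietary intervention in out-patients". The objective in section 2 begins "To evaluate the effect of brown rice or white rice-based diet intervention on glycemic" and goes on to lipids and vascular function. Neither it nor section 4 names acceptability or harms.

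**Continuation of the study.** Section 8 asks the principal investigator to determine "whether continuation of the study can be justified when significant information regarding quality, safety are newly recognized".

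**The concern.** A SAP can analyse only what has been collected, and this protocol fixes the collection route for adverse events. That route starts when someone recognises an event and ends in the chart. The trial is open-label, and patients new to brown rice may report digestive or other complaints more readily, or be asked about them more often, than patients given white rice. The reverse is also possible. Either way, recording could differ between arms for reasons other than the diet, and nothing in the plan makes the two arms comparable.

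For acceptability, the hypothesis concerns the test food, but the one stated tolerability assessment takes place before anyone receives that food. At stake are the safety report by arm and the support for one stated part of the hypothesis. The endothelial result is not at stake.

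**Working it through.** The protocol gives no figure for harms, so there is none to reproduce. The check is mainly a comparison of what is collected, and when, followed by some short arithmetic on size.

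**1. What each source captures after randomisation**

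| Source | Captures | Does not capture |
|---|---|---|
| Section 9.4 | Events recognised by investigators, in the chart | A routine enquiry; a CRF entry |
| Section 3.9 | Medication changes due to hypoglycemia, on the CRF, in run-in and intervention | Episodes without a medication change; the energy control period |
| Section 7 | Reason and date of discontinuation, including difficulty with the diet | Symptoms in patients who stay |
| Section 3.7 | Three-day photographed dietary records | Harms; most meals |
| Section 4.2, item 9 | Questionnaire on eating behaviour and psychosomatic state | Harms, as far as described |
| Figure 2, rows that can be read | Weight, blood, urine, vascular tests, meal test and others | Any adverse-event or tolerability row |

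The Figure 2 footnote takes certain weight and blood-test entries from charts. It does not plan chart extraction of adverse events.

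**2. Order of tolerability assessment and exposure**

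- Run-in, 4 to 8 weeks: standard diet, tolerability assessed.
- Randomisation.
- Intervention, 8 weeks: first exposure to the assigned pouches, no tolerability assessment stated.

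Since prior brown rice eaters are excluded, run-in tolerability carries no information on brown rice.

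**3. Coverage of the dietary record**

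Inputs: 21 meals per week, hence 3 per day, for 8 weeks (sections 3.4 and 3.6.2). The number of records taken during the intervention is not stated, so one is assumed.

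- Meals in the period: 21 × 8 = 168.
- Meals in one record: 3 × 3 = 9, or 9/168 = 5.4%.
- Pouch meals instructed: 10 × 8 = 80 per participant. No count of those eaten is specified.

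**4. Size in an arm of 15 (section 3.2)**

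- One patient's event missed: 1/15 = 6.7 percentage points.
- Zero events, upper two-sided 95% exact limit, 1 − 0.025^(1/n): for n = 15, 1 − 0.025^(1/15) = 21.8%.
- After the planned 14% loss (section 3.2.1), 15 × 0.86 = 12.9, about 13: 1 − 0.025^(1/13) = 24.7%.
- With no events in one arm of 15, the two-sided Fisher test falls below 0.05 only from 5 events in the other: 5/15 = 33%.

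The last three lines assume complete capture. They limit what any harms comparison here could show and do not measure the effect of the recording route.

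**The case against.** The strongest case against is that the protocol collects more than sections 9.4 and 3.6.1 suggest. Reasons for discontinuation (section 7), dietary records during the intervention (section 3.7) and the questionnaire (section 4.2) all give data by arm during or after exposure. Liver enzymes are secondary outcomes, so some laboratory safety data exist as well. CRF content and safety tables are often settled in other documents. Section 9.4 sits among the patient-protection provisions and may be read as a duty of care rather than a data plan. Section 3.6.1 never claims to measure tolerability of brown rice, and acceptability appears in the Background, not as an objective.

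Much of this stands, and it rules out several stronger readings that a reader might infer:

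- *The trial cannot compare harms by arm.* Not supported. There are 30 patients at one hospital, and their charts could be abstracted by arm. The result would be less reliable, not absent.
- *The acceptability hypothesis rests only on data from before exposure.* Not supported, given sections 3.7, 4.2 and 7.
- *The continuation decision in section 8 has nothing systematic to draw on.* Not supported. That section is not limited to data on trial forms, and the principal investigator also sees events and discontinuations directly.
- *Section 3.6.1 is wrong about tolerability.* Not supported. It describes a standard-diet run-in, and the text can stay.
- *A by-arm harms analysis has been omitted.* It could be in a SAP that is not shown, so its absence is no finding.

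What the objection does not remove is the fixed collection route. The listed sources see problems that end participation, or food intake, or behaviour. None is described as recording symptoms in patients who continue. The protocol asks for CRF entry where it wants it (section 3.9), and for adverse events it names the chart instead.

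**Conclusion.** The point holds as a weakness in data capture. After randomisation there is no stated systematic CRF collection of adverse events, hypoglycemia reaches the CRF only through a medication change, and no outcome is tied to the acceptability hypothesis. Harms by arm would rest on chart entries made on recognition in an open-label trial, and acceptability on indirect data.

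The effect is moderate. It does not touch the primary endothelial comparison. The direction and size of any differential recording cannot be derived from the protocol; unevenness between arms is a plausible risk, not a certainty. Even perfect recording would give only a descriptive comparison at this sample size. The change is still worth making, because it is cheap and less open to bias than the stated route.

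The conclusion assumes that no separate CRF specification already requires these entries, and that the rows of Figure 2 that can be read are complete. The visit headings of that table are not visible; months 0, 2 and 4 are taken from section 4.

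**What to change.** These changes concern data capture only and leave clinical management as it is.

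1. **Section 9.4.** Keep the present duty, and add that every adverse event and every hypoglycemia episode, whether or not a drug is changed, is recorded on the CRF. Ask the same scripted question in both arms at the existing month 0, 2 and 4 visits. The month 0 answer serves as the baseline.
2. **Section 4.2 and Figure 2.** Add one descriptive by-arm item with four parts: adverse events, tolerability of the assigned rice, diet-related discontinuations, and pouch meals eaten against the instructed 10 per week. Add the matching row to the schedule.
3. **Reporting.** State that this item is descriptive, with counts and exact intervals and no formal test of harms.

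The cost is one CRF page, one descriptive table and a few minutes per visit. Reported event counts may be higher than under chart recording, because patients will be asked. No visit, sample or patient is added.

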**9.5 Cost for patients**

This study will be funded by the Department of Medicine, Shiga University of Medical Science (SUMS), and Sunstar Inc. All cost for additional tests and test meals are covered by research expenses.

**9.6 Handling of personal information**

All personal data for this research will not be used for other than this study and protected.

**10 Publication**

The results of this study will be published at medical journal and/or annual meeting of scientific association. Personal information will be protected also at this moment.

**11 Research Institutions**

**11.1 Medical Institutions**

　　Shiga University Hospital

**11.2 Provider of test meal**

　　Sunstar Inc.

**11.3 Clinical laboratory services**

　　SRL, Inc (blood, urine)

Techno Suruga Lab (bacterial flora)

JCL Bioassay Corporation (lipid metabolites)

**12 Funding**

This study will be funded by the promotion grants to the Department of Medicine, Shiga University of Medical Science (Shogaku-kifu), and Sunstar Inc.

**13 Conflict of Interest**

Potential conflict of interest will be reported based on the instruction of journal and association.

**16 Date of protocol fixation**

September 15, 2011

Updated date: April 6, 2012
